#### Intervention 1 – Corticosteroids

Treating clinicians will be advised to prescribe 50 mg prednisolone daily for 7 days. See Additional file 2 for details of specific contraindications for corticosteroid therapy.

Patients with diagnosed diabetes will be routinely monitored for hyperglycaemia (see Data monitoring section) and managed at the discretion of the treating team in accordance with existing institutional procedures and practices. All admitted patients have blood glucose levels measured in the emergency department, and ongoing random blood glucose monitoring may also be implemented for other patients thought to be at risk of hyperglycaemia at the discretion of the treating team. Any variation to the dose and duration, such as use of tapered dosage, and time from admission until first dose will also be recorded. Alternative medical reasons given for non-prescription of corticosteroids, or reduced duration of administration, will be noted.

#### Intervention 2 – Early switch to oral antibiotics

Guideline-consistent prescription of initial antibiotic therapy and constrained parenteral antibiotic duration (using pre-defined stopping rules) will be provided in the best-practice group [17, 18].

Current institutional general internal medicine antibiotic prescribing practice aims to follow an institutional guideline based on the Australian Antibiotic Guidelines [38]. Patients are stratified as having mild, moderate or severe disease using standardised pneumonia severity criteria. Our institution uses the CORB score, based on its ease and feasibility of use, and it having the highest predictive value for poor outcomes [10]. Based on CORB, most inpatients receive either intravenous penicillin and doxycycline, or roxithromycin (mild or moderate disease), or ceftriaxone and azithromycin (severe disease).

Patients will be switched from intravenous to oral therapy according to the specific criteria for clinical improvement, which will be assessed on a daily basis by the community-acquired pneumonia service using a standardised checklist (also commonly referred to as ‘stopping rules’, see Additional file 2). Essentially, for switching to oral antibiotics, patients must be able to maintain oral intake, have stable vital signs, stable SpO_2_ and no evidence of septic metastases or major exacerbated comorbidities [18].

Any reason for alternative antibiotic selection (such as allergy or advice from an infectious diseases consultant) will be noted.

#### Intervention 3 – Early mobilisation

Physiotherapist-led early (<24 h) and progressive mobilisation will be provided daily, and is defined as movement out of bed with change from horizontal to upright position for at least 20 min during the first 24 hours of admission to a general internal medicine unit (a minimum score of 2 on the Intensive Care Unit Mobility Scale [39]), and progressive movement each subsequent day [16]. See Additional file 2 for intervention details, including specific contraindications and stopping criteria for daily mobilisation.

Exercise tolerance (total distance mobilised before requiring a rest, and total distance mobilised during the session) will be recorded for each session, as will any reason why early or progressive movement is not achieved and any adverse events during physiotherapy sessions.

#### Intervention 4 – Malnutrition risk screening with targeted nutritional therapy

Standardised malnutrition screening, using the Malnutrition Screening Tool [40] and measurement of patient body weight (in kilograms) will be completed within 24 hours of admission to a general internal medicine unit. The Malnutrition Screening Tool score will guide implementation of nutritional therapy as follows [41]:0–1: No nutrition therapy intervention indicated2–3: Initiation of a high-energy high-protein diet by nursing staff4–5: Referral to the institutional Dietetics Service for urgent review and implementation of an individually tailored malnutrition intervention

Reasons for non-compliance with the malnutrition screening protocol will be noted.

#### Control group

During the non-interventional control periods (as determined by the stepped-wedge rollout schedule), patients admitted with community-acquired pneumonia under eligible general internal medicine units will receive usual care at the discretion of the treating general internal medicine multidisciplinary team. Ultimate responsibility for treatment decisions is generally made by a supervising general internal medicine consultant physician, who reviews patients on the morning after admission and on supervisory ward rounds conducted three times per week. Junior medical staff (registrar level) are also involved in day-to-day medical decision-making but allied health practitioners (physiotherapists and dieticians) are generally only involved if there has been a formal referral process initiated by a member of the treating medical or nursing team.

Pre-trial standard care at the study institution (auditing conducted in 2015) consisted of the following proportions of patients with community-acquired pneumonia receiving: corticosteroids (43%), a guideline-compliant antibiotic (65%) and physiotherapy (including early mobilisation) (63%; median time to initiation, two days). No parenteral antibiotic stopping rules are in place (median duration 3 days), while malnutrition risk screening in inpatients across all health-service patients is 72%.

All other aspects of patient care, including fluid delivery, use of lines and drains, general nursing care and discharge planning, will be provided at the discretion of the general internal medicine teams, as per routine institutional practice or protocols.

### Blinding

Clinicians providing patient interventions cannot be blinded, although participants are effectively blinded, owing to the waiver of consent. All primary and secondary outcome measures are routinely collected within the organisation by staff not involved in delivery of the intervention, who will be unaware of participant group allocation. There is therefore little or no potential risk of bias in outcome assessments. A statistician blinded to the allocation sequence will perform data analysis.

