### Secondary trial outcome measures

Secondary outcome measures comprise routinely collected institutional data and include:Inpatient mortality30 day and 90 day readmission rates and mortalityAdmission to the intensive care unit from inpatient wards and requirement for and duration of mechanical ventilationTotal individual per-separation hospital clinical costing, as determined by the institutional dedicated clinical costing unit using the Power Performance Manager™ software platform (Power Health Solutions, Adelaide, Australia)Protocol adherence (proportion of evidence-based treatments delivered in each group; proportion of patients receiving the whole bundle; reasons for protocol adherence failure)Serious adverse events (including the incidence of in-hospital hyperglycaemia requiring new insulin prescription, adverse drug reactions where it is required that the drug use is stopped, falls or clinical deterioration requiring urgent medical review during early mobilisation), other adverse events and clinical complications (Table 2) occurring prior to admission, during inpatient stay or requiring re-presentation to hospital within 30 days.

**Table 2 Tab2:** Reporting of serious adverse events, adverse events and complications

Complication group	Complication
Pneumonia-associated complications	Respiratory failure requiring intubation
	Hypotension requiring vasopressors
	Empyema *Defined as: documented in registrar admission assessment, radiologist chest X-ray report or medical discharge summary*
	Acute respiratory distress syndrome *Defined as: documented in registrar admission assessment, radiologist chest X-ray report or medical discharge summary*
	Pleural effusion *Defined as: diagnosed on radiologist chest X-ray report*
	Increased confusion from baseline
Other adverse events	Death from any cause
	Fall with fracture
	Cardiac decompensation *Defined as: documented in registrar admission assessment, radiologist chest X-ray report or medical discharge summary*
	Cardiac event *Defined as: diagnosed episode of cardiac ischaemia or new cardiac arrhythmia*
	Acute stroke *Defined as: documented in registrar admission assessment, radiologist report or medical discharge summary*
	Thromboembolic event *Defined as: pulmonary embolus or deep vein thrombosis documented in registrar admission assessment, radiologist report or medical discharge summary*
	Confirmed or suspected gastrointestinal bleeding

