### Data management

All data will be collected through existing routine processes and captured in the patient electronic medical record stored on the password-protected hospital admission information systems (iPM / EDIS v.EDISAPAC 15.1.0 [CSC, Tysons, Virginia USA] and Bossnet [Core Medical Solutions, Rose Park, South Australia]). Data from the electronic medical record will be extracted by study investigators where required throughout admission and after discharge from hospital.

Data will be extracted from iPM and EDIS systems after the patient has been discharged and then separately entered into a dedicated REDCap (research electronic data capture) database [43] hosted at the University of Melbourne, Melbourne, Australia. An investigator will randomly audit data collection of one patient per each ten recruited to ensure data quality and data entry will be randomly checked and cleaned by an investigator, either a chief investigator or an investigator supervised by a chief investigator. On publication of the trial, the database will be made available for independent analysis pending the necessary ethical approvals if requested.

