### Data monitoring

Adverse events and adverse drug reactions that are considered to be associated with the delivery of the community-acquired pneumonia service protocolised interventions will be reported to the principal investigator within 72 hours. Patients receiving routine corticosteroids as a component of the community-acquired pneumonia service interventions will be reviewed daily and records will be kept of any hyperglycaemia requiring new insulin treatment. A log of adverse events and adverse drug reactions will be kept and reported to the project steering committee at quarterly meetings, and to the Melbourne Health Human Research Ethics Committee at 3 month intervals.

Serious adverse events and suspected unexpected serious adverse reactions will be reported to the Melbourne Health Human Research Ethics Committee within 72 hours. These may include (but are not limited to):Unexpected deathSerious drug-related adverse event (directly linked to either antibiotic or corticosteroid dose) where it is required that the drug is stoppedA fall with associated patient or clinician injury during physiotherapyPatient deteriorating clinically within 60 min of a physiotherapy session requiring a medical emergency team call or code blue (as defined by institutional procedures)

The project steering committee will meet quarterly to report enrolment numbers, protocol adherence or violations and adverse events and report these to the human research ethics committee. A data monitoring committee was not deemed necessary because outcome measures (e.g. length of stay) are (1) objective, (2) unambiguous and (3) collected through existing routine, validated measures (and therefore not prone to data integrity issues).

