### Duration and timeline

It is anticipated that the study period will be completed in July 2017 and that data collection will be completed and analysed, and the manuscript prepared for submission, by December 2018. The final manuscript will be written in accordance with the relevant CONSORT statements and extensions [30].

Trial design and methods are summarised in Table 3.

**Table 3 Tab3:** World Health Organization Trial Registration Data Set for IMPROVE-GAP trial

Data category	Information
Primary registry and trial identifying number	www.ClinicalTrials.gov, NCT02835040
Date of registration in primary registry	22 May 2016
Secondary identifying numbers	Not applicable
Trial protocol version	This is Version 3 of the protocol and was enacted on 24 August 2016
Source of monetary or material support	The HCF Research Foundation (AU $300,000)
Primary sponsor	The HCF Research Foundation
Secondary sponsor	Not applicable
Contact for public queries	HK, [contact]
Contact for scientific queries	HK, [contact]
Public title	IMPROVing Evidence-based treatment Gaps and outcomes in community-Acquired Pneumonia (IMPROVE-GAP).
Scientific title	IMPROVE-GAP: Evaluating the impact of a new model of care designed to improve evidence-based management of community-acquired pneumonia
Country of recruitment	Australia
Health condition or problem studied	Community-acquired pneumonia
Intervention	Active comparator: Evidence-based bundle of care (specifically: corticosteroids, early mobilisation, guideline-compliance antibiotic and early switch to oral antibiotic therapy, malnutrition risk screening and targeted nutritional therapy) Placebo comparator: Usual inpatient care
Key inclusion and exclusion criteria	Ages eligible for study: ≥ 18 yrs Sexes eligible for study: Both Accepts healthy volunteers: No Inclusion criteria: All adults admitted to the institution under a general internal medicine unit with community-acquired pneumonia (meeting a standardised community-acquired pneumonia definition) Exclusion criteria: (1) patients where a decision is made to implement palliative care on admission; (2) existing enrolment in a clinical trial.
Study type	Type: Investigator-initiated, interventional, pragmatic, study Allocation: Concealed randomisation Intervention model: Stepped-wedge rollout Masking: Patient and assessor blinded Primary purpose: Treatment Phase: Phase IV
Date of first enrolment	01/08/2016
Target sample size	Minimum 640 patients
Recruitment status	Recruiting

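### The blinding statement does not hold for adverse events and protocol adherence, so part of the harm comparison is open to detection bias

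*Protocol article*

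**What the plan says.** **The claim.** Under Blinding: "All primary and secondary outcome measures are routinely collected within the organisation by staff not involved in delivery of the intervention". The same sentence says these staff will be unaware of group allocation. The section then concludes: "There is therefore little or no potential risk of bias in outcome assessments". Table 3 has the matching entry "Masking: Patient and assessor blinded", with no outcome excepted.

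**What counts as a secondary outcome.** Secondary trial outcome measures lists protocol adherence and then safety: "Serious adverse events (including the incidence of in-hospital hyperglycaemia requiring new insulin prescription", followed by drug reactions that require stopping the drug, falls or deterioration during mobilisation, other adverse events and the complications in Table 2. The word all in the blinding statement therefore covers them.

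**How these outcomes are recorded.**
- Intervention 3 has the details of each mobilisation session recorded, including "any adverse events during physiotherapy sessions".
- Data monitoring says that patients receiving corticosteroids as part of the service "will be reviewed daily and records will be kept of any hyperglycaemia requiring new insulin treatment".
- Data monitoring ties 72-hour reporting to the principal investigator to "Adverse events and adverse drug reactions that are considered to be associated with the delivery of the community-acquired pneumonia service protocolised interventions".
- Data management says: "Data from the electronic medical record will be extracted by study investigators where required throughout admission", and also after discharge.
- Table 1, item 11, has the pneumonia team monitoring adherence through its daily contact.

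**The concern.** The blinding claim suits outcomes that administrative systems generate whether or not anyone is looking, such as time of discharge, death or cost. It does not suit outcomes that exist in the data only if someone notices an event and writes it down, when those observers and recorders include the people delivering the intervention, whom the protocol itself says cannot be blinded.

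Two things are at stake. First, the trial would report assessor blinding for outcomes that did not have it. Second, the harm comparison could not be read cleanly. If more events appeared under the intervention, a true excess could be put down to closer watching, and a spurious one could count against the service. The Data monitoring section uses the same premise, that outcomes are objective and routinely collected, to explain why no data monitoring committee was appointed. That premise describes length of stay well and these events less well.

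**Working it through.** The document gives no event rates or recording probabilities, so there is no stated figure to reproduce. The check sets the sections side by side.

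**1. Is the statement contradicted?** It makes two assertions about every secondary outcome: collectors are outside the intervention, and they do not know the allocation.
- *Session events.* Falls, deterioration and ceased mobilisation during physiotherapy are Table 2 outcomes. They are recorded at sessions led by a physiotherapist, and the service is itself physiotherapist-led (Trial intervention). The natural recorder is the person delivering the treatment.
- *Hyperglycaemia requiring new insulin.* The daily review and record are stated for service corticosteroid recipients only.
- *Adherence.* The service assesses the criteria for switching antibiotics daily with its own checklist (Intervention 2) and monitors adherence (Table 1, item 11).
- *Extraction.* Study investigators take data from the record, and notes that contain service entries can show which condition the patient was in.

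Both assertions fail for adverse events and adherence.

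**2. Is recording heavier in one condition?**

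| | Intervention periods | Control periods |
|---|---|---|
| Added rounds | Daily by the service, seven days a week | None described |
| Usual medical review | Treating team continues | Consultant the morning after admission, then three rounds a week; registrars day to day |
| Physiotherapy | Daily, details recorded per session | Generally on referral; 63% received it in the 2015 audit, median start two days |
| Corticosteroids | Daily review, insulin events recorded | 43% received them in the audit; no matching review described |
| Events taken from medical record | Yes | Yes |
| Four-hourly vital signs | Yes | Yes |

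The last two rows are common to both. The others describe more observation and charting under the intervention.

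**3. Which outcomes are exposed?** Those that depend on looking or charting: insulin-requiring hyperglycaemia, drug reactions and events during physiotherapy. Not exposed are length of stay, mortality, intensive care and ventilation, and costs, which the At discharge and 30 and 90 day sections take from the data warehouse. Nor are Table 2 rows defined by a radiology report, such as pleural effusion. No section describes service surveillance for confusion, so that row is not counted.

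**4. Direction and scale.** With equal true risk in both conditions,

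apparent risk ratio = (probability recorded, intervention) / (probability recorded, control).

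All of these probabilities are assumptions, for illustration only:
- equal capture, 0.90/0.90 = 1.00
- 1.00/0.90 = 1.11
- 0.90/0.70 = 1.29
- 0.95/0.60 = 1.58

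The ratio exceeds 1 whenever capture is better under the intervention. Nothing in the document selects among these values.

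**The case against.** The case on the other side is substantial.

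- **Collection is common to both conditions.** The Daily during admission section collects serious adverse events, adverse events and complications from the medical record for all enrolled patients. It also describes four-hourly vital signs as routine care and daily review of clinically indicated glucose readings. Intervention 1 has patients with diagnosed diabetes monitored routinely and an emergency department glucose for every admission. Registrars are involved day to day in control periods. It would be wrong to say that control patients go unobserved.
- **Several outcomes have an action threshold.** A new insulin prescription or a stopped drug would ordinarily be charted in either condition. Closer review can still prompt more of these actions, but the gap may be small.
- **Some rows are conditional on exposure.** Physiotherapy events are percentages of sessions delivered. That corrects for the number of sessions, not for how completely each is recorded.
- **Safety is not among the stated secondary objectives**, and no specific comparative test of harm is given. It is nevertheless listed among the secondary outcomes, and Statistical methods applies one model to primary and secondary analyses.
- **Detailed extraction rules may be in material not shown.** That would answer an omission. It does not answer a positive statement that other sections contradict.

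A reader might infer that the harm comparison is shown to be biased, or that a particular inflation can be attached to it. The document supports neither. It shows a route for bias and a direction, and the common record-based collection could leave the effect small.

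**Conclusion.** The point holds in this form. The Blinding statement and the Table 3 masking entry are contradicted by other sections for adverse events and protocol adherence. For events that depend on looking or charting, the comparison between conditions is open to detection bias towards apparent harm under the intervention. This rests on reading the described daily review and session recording as additional to usual care, with no counterpart in control periods; none is described.

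The size cannot be determined. The illustrative ratios of 1.00 to 1.58 rest wholly on assumed recording probabilities and are not estimates. The primary outcome and the other warehouse outcomes are not affected, so the main efficacy conclusion does not depend on this point. What changes is what the trial may claim about blinding and how far its safety comparison can be interpreted.

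**What to change.** 1. Limit the Blinding statement, its conclusion about bias and the Table 3 masking entry to outcomes taken from the data warehouse. State that adverse events and adherence are recorded and extracted unblinded.
2. Base the comparative safety analysis on record sources that are present in both conditions and already in use: medication and insulin orders, radiology reports, registrar admission assessments, discharge summaries and ICD-10 codes. Extract them with one checklist for every patient.
3. Report events logged by the service (session logs, daily corticosteroid review) descriptively for the intervention condition. They remain available for ethics reporting.

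**Cost.** The first change is wording. The second needs one common form for records that are already reviewed for every enrolled patient. Because the trial is recruiting, it would also have to be applied to patients already enrolled. No new data source is needed. Minor events seen only by the service drop out of the between-group comparison. A common checklist does not blind the extractor, and closer review could still lead to more insulin orders, so some risk of bias remains and should be acknowledged in the report.

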### Withdrawal from trial

Participants will be withdrawn if they are transferred to another unit (e.g. specialist respiratory, cardiology or surgical) or another health service within 48 hours of admission, or are no longer considered to meet the community-acquired pneumonia case definition on consultant review. All withdrawals and reasons will be reported.

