### Ascertainment, enrolment and waiver of consent

Ascertainment will be conducted prospectively to identify eligible participants in real time ensuring employment of identical methods of ascertainment for both control and intervention groups. A community-acquired pneumonia service team member will attend each general internal medicine morning clinical handover meeting to identify new admissions with possible respiratory infection from the previous 24 hours. Either the chief medical registrar or treating medical registrar will subsequently review the medical record and chest X-ray (for evidence of a new infiltrate, as per requirements of the standardised case definition) of potential participants to assess eligibility. Those meeting this case definition [34] and eligibility criteria will be enrolled. In situations where the chest radiograph or community-acquired pneumonia diagnosis are not definitive, the treating medical consultant will determine eligibility.

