#### Daily during admission (clinical monitoring)

Circumstances necessitating withdrawal of a participant from the study after enrolment but within 48 hours of admission to a general internal medicine unit will be recorded.

The following variables will be collected from the medical record and reported for all enrolled patients: any serious adverse events, adverse events or clinical complications (see Table 2), any decision to palliate, adherence to protocol for Interventions 1 to 4 (as listed previously).

Daily vital signs (SpO_2_, supplementary oxygen requirements, heart rate, respiratory rate, blood pressure, temperature) will be measured every 4 hours as per routine clinical care and used to ascertain the switch to oral from intravenous antibiotics.

Blood glucose readings as clinically indicated and requested by treating team, and oral intake status (ability to tolerate oral medications and absence of gastrointestinal problems that may affect drug absorption) will also be reviewed daily.

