### Statistical methods

In a stepped-wedge design clusters contribute different amounts of time to the intervention and control periods, making traditional measures of covariate balance between intervention arms difficult to use [44]. In this study, we will use a method to assess covariate balance by calculating a weighted average of each baseline characteristic for control and intervention periods; cluster [16] characteristics will be weighted by the amount of person-time they contributed to control and intervention periods (i.e., a cluster that crossed over in Step 2 contributed baseline covariates to two control periods (Steps 0–1) and three intervention periods (Steps 2–4)) [45].

Demographic and clinical characteristics of participants in the study will be described using means and standard deviations for continuous variables, and frequencies and percentages for categorical variables.

Primary and secondary analyses will be as randomised using a multi-level, mixed effects generalised linear model. The effect of the intervention and time period will be considered as fixed effects while the effect of treating general internal medicine unit and patient will be considered as random effects. This will include adjustment for block and time period of the design, seasonal variation in the outcomes (based on the previous 2 years of data), age and sex of the patient admissions [28, 30, 31].

We will make every effort to minimise missing outcome data at each wave. We will report the amounts of missing data according to published recommendations [46]. In addition, sensitivity analyses will be conducted to assess the robustness of the missing data assumption made in the primary analysis. A detailed analysis plan will be developed for secondary and sensitivity analyses. Statistical analyses will be carried out using Stata® (StataCorp. College Station, Texas USA).

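### Enrolled patients are withdrawn on post-allocation decisions by unblinded clinicians, and nothing says they stay in the analysis; this conflicts with an as-randomised analysis and risks selection bias of unknown size and direction

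*Protocol article*

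**What the plan says.** The Withdrawal from trial section gives two grounds for removing someone already enrolled. The first is early transfer, with the clock running from admission: "Participants will be withdrawn if they are transferred to another unit (e.g. specialist respiratory, cardiology or surgical) or another health service within 48 hours". The second covers those who "are no longer considered to meet the community-acquired pneumonia case definition on consultant review". The section's only safeguard is "All withdrawals and reasons will be reported".

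Daily during admission (clinical monitoring) confirms the timing, and that the person leaves the study. The item to be noted there is "Circumstances necessitating withdrawal of a participant from the study after enrolment but within 48 hours of admission to a general internal medicine unit".

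Blinding states "Clinicians providing patient interventions cannot be blinded". Statistical methods states "Primary and secondary analyses will be as randomised using a multi-level, mixed effects generalised linear model".

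Under Primary outcome measure, length of stay runs from arrival in the emergency department to discharge from the health service, and is routinely held for every inpatient. ICU admission from the wards and mechanical ventilation are secondary outcomes.

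**The concern.** A unit's condition in any week is set by the rollout schedule, so a transfer or revised diagnosis after enrolment is a post-allocation event. If it removes the patient from the analysed set, that set is partly chosen by clinicians who know the condition. The comparison is then no longer the one that randomisation protects.

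Differential withdrawal is plausible. Intervention units have an additional team rounding daily on study patients. Usual care is described as consultant review on the morning after admission and three supervisory rounds a week. More contact gives more occasions to reconsider a diagnosis or arrange a move.

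The diagnosis ground carries no time limit in the Withdrawal section. If it is open-ended, a longer stay gives more opportunity to be withdrawn, and exclusion would depend on the primary outcome itself.

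The article's defences do not cover this. The Blinding section addresses outcome assessment. The Discussion's selection-bias argument addresses how patients reach a unit, and its attrition argument relies on routine outcomes, which make dropping patients unnecessary in most cases.

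**Working it through.** **1. The passages side by side**

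| Question | What the article gives |
|---|---|
| When does withdrawal happen? | After enrolment, from the study (Daily during admission) |
| Is the condition known by then? | Yes, fixed by the rollout schedule; clinicians unblinded (Blinding) |
| Which patients are analysed? | As randomised (Statistical methods) |
| Are withdrawn patients kept? | Not stated; reporting only (Withdrawal from trial) |
| Is their length of stay available? | Yes, collected for all inpatients (Primary outcome measure) |

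The first four rows cannot all hold unless withdrawal means something less than removal from the analysis, and the article does not say so.

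**2. Power is not the issue**

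The article's figure is 75% power with 640 patients, 36% v 20%, intra-cluster correlation 0.01. A Hussey-Hughes calculation (8 units, 5 periods, 80/5 = 16 per unit-period, two-sided 5%) gives 82.3–83.9% with pooled or unpooled variance and 77.1–77.5% with control-arm variance. Only control-arm variance with a t reference on 34 df comes to about 75% (74.7–75.1%). Dropping 10% of patients without replacement lowers power to about 79% (pooled) or 74% (control-arm). The loss is modest, so the question is bias.

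**3. Size of the bias**

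Inputs:
- p = 0.36, the long-stay proportion in the sample-size section, taken in both conditions (no true effect).
- w = proportion withdrawn, and q = long-stay proportion among those withdrawn. Both are assumed; the article gives neither.
- Withdrawal acts alike in all periods and units, so a simple difference stands in for the model estimate.

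Proportion with a long stay among those retained = (p − w·q)/(1 − w).

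Example: w = 0.20, q = 0.70 gives (0.36 − 0.14)/0.80 = 0.275; w = 0.10 gives (0.36 − 0.07)/0.90 = 0.322; difference −4.7 points.

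| Withdrawn, control | Withdrawn, intervention | q | Control retained | Intervention retained | Difference (points) |
|---|---|---|---|---|---|
| 5% | 15% | 0.70 | 34.2% | 30.0% | −4.2 |
| 5% | 15% | 0.50 | 35.3% | 33.5% | −1.7 |
| 5% | 15% | 0.20 | 36.8% | 38.8% | +2.0 |
| 10% | 20% | 0.70 | 32.2% | 27.5% | −4.7 |
| 10% | 20% | 0.50 | 34.4% | 32.5% | −1.9 |
| 10% | 20% | 0.20 | 37.8% | 40.0% | +2.2 |
| 10% | 10% | 0.70 | 32.2% | 32.2% | 0 |
| 10% | 5% | 0.70 | 32.2% | 34.2% | +2.0 |

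With more withdrawal under intervention, the range is −4.7 to +2.2 points, against a planned 36 − 20 = 16. Swapping which condition withdraws more reverses the sign. Equal rates with equal q give zero. Equal rates alone are not enough if the kind of patient withdrawn differs by condition. The range illustrates the mechanism and is not a bound.

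**The case against.** The strongest reply is that the conflict is inferred. No sentence says that withdrawn patients' data are discarded, adverse events and adherence are to be collected for all enrolled patients, and analysis sets are often defined in an SAP, which is not shown here. The CONSORT figure is also not shown. This stands in part: exclusion is the natural meaning of withdrawal from a study, not an explicit statement. But the protocol itself fixes the rule, and the article defers only secondary and sensitivity analyses to a further plan.

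It is also fair that a consultant who dislikes a component has little need to change the diagnosis. Item 9 of the intervention table lets consultants vary care, with non-adherence recorded. This weakens the motive for relabelling but does not remove the effect of unequal contact.

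Several stronger readings are tempting and are not supported:
- **The bias favours the intervention because withdrawn patients are sicker.** Patients moved to another health service have short recorded stays, and the table shows that the sign can go either way.
- **ICU events are lost.** The outcome concerns admission "to the intensive care unit from inpatient wards and requirement for and duration of mechanical" ventilation, and ICU is not among the example units in the transfer rule. The article leaves open whether an early ICU move counts as a transfer.
- **No patient need be lost because every outcome is in the data warehouse.** Adherence and adverse events come from the medical record. The Discussion says readmissions elsewhere are not captured, and costs are limited to this health service.
- **The treating consultant decides withdrawal.** The statement that "the treating medical consultant will determine eligibility" concerns uncertain cases at entry. The withdrawal rule says only that a consultant reviews, and does not say who decides transfers.
- **An analysis of all pneumonia-coded separations would settle the matter.** Coding at discharge also follows allocation, and that set would include patients the protocol excludes.

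**Conclusion.** The point holds as a conflict on plain reading, with a risk of selection bias. Enrolled patients leave the study on post-allocation events involving unblinded clinicians, nothing keeps them in the analysis, and the analysis is declared to be as randomised.

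The documents do not show that bias will occur, or which way it would run. The illustrated range of about −5 to +2 points rests on assumed withdrawal rates of 5–10% in control and 15–20% in intervention periods, and on 20–70% long stays among those withdrawn. Even the largest illustrated value is well below the planned 16 points. It could still matter if the true effect is smaller than planned.

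**What to change.** - State that transfer or a revised diagnosis does not remove a patient from the analysis. Every enrolled patient stays in the primary and secondary analyses under the unit and period of admission, using the routinely collected length of stay, mortality, readmission and cost data.
- Report withdrawals and reasons by condition and period.
- Use the set without withdrawn patients only as a sensitivity analysis.
- Add a sensitivity analysis for patients transferred to another health service, whose length of stay is truncated and whose readmission and cost data are incomplete.
- Reconcile Withdrawal from trial with Daily during admission on whether the 48-hour limit applies to revised diagnoses.
- Reconcile Withdrawal from trial with Secondary trial outcome measures on whether an early ICU move counts as a transfer to another unit.

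The cost is wording and two sensitivity analyses. Some patients without pneumonia will stay in and dilute the effect slightly, and external transfers will enter the primary analysis with short recorded stays. Both downsides should be stated. The planned 640 patients are unaffected.
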